#### Informed consent

The consent process will provide information about the study to a prospective participant and will allow adequate time for review and discussion prior to his/her/their decision. The PI will review the consent with the patient or their LAR and answer questions. The prospective participant will be told that being in the trial is voluntary and that they may withdraw from the study at any time, for any reason. All participants (or their LAR) will read, sign, and date a consent form before undergoing any study procedures. Consent materials will be presented in participants’ primary language. A copy of the signed consent form will be given to the participant.

The consent process will be ongoing. The consent form will be revised when important new safety information is available, the protocol is amended, and/or new information becomes available that may affect participation in the study.

### Interventions

#### Intervention description

Patients will be randomized 1:1:1:1 to receive one of 3 doses (0.5, 2.5, or 5 mg/kg) of Somazina® citicoline solution for injection (Ferrer Internacional, S.A., Barcelona, Spain) diluted in sterile normal saline or placebo (sterile normal saline). Somazina® is approved by the European Medicines Agency for use with a prescription in Europe. Patients will be treated with study agent every 12 h for up to 5 days.

Citicoline will be provided in sterile, single-use, Type I neutral glass ampoules containing 1000 mg active pharmaceutical ingredient (citicoline) dissolved in 4 ml water (final concentration 250 mg/ml), with HCl added to normalize pH; no other excipients are present. Study ampoules will be shipped from Ferrer directly to the IDS at OSU WMC and stored at room temperature in the dark. The immediate package of this investigational new drug will be labeled with the statement “Caution: New Drug – Limited by Federal (or United States) law to investigational use.”

Study drugs will be prepared on the day of use by a research pharmacist in the IDS at OSU WMC. Citicoline solution will be diluted in USP-compliant sterile normal saline to a final volume of 20 ml containing the appropriate total daily dose for each patient (1, 5, or 10 mg/kg/day, based on their ID number). Doses will be rounded to the nearest 0.1 ml per standard rounding rules. Two 10-ml aliquots will then be prepared in sterile disposable syringes labeled with the patient ID number for administration 12 h apart and then kept refrigerated. Unused undiluted or diluted citicoline will be discarded by the IDS pharmacist and documented as such. Placebo controls will receive 10 ml USP-compliant sterile normal saline every 12 h for 5 days.

Each 10 ml dose of test agent will be delivered by nursing staff as a slow i.v. bolus over 3–5 min and immediately documented in the EMR. EMRs will be reviewed daily by the clinical trial coordinator to ensure test agent administration has occurred and been documented.

#### Criteria for discontinuing or modifying allocated interventions

No modifications to the test agent dose or frequency will be permitted during the study period. Study therapy may be prematurely discontinued for any participant for any of the following reasons: (1) SAEs occur that, in the view of the attending clinician, study investigator, or PI, may be attributable to citicoline; (2) The PI believes that the study treatment is no longer in the best interest of the participant; or (3) The Data Safety Monitoring Board (DSMB) will make a determination of futility or potential for harm to the patient(s).

#### Strategies to improve adherence to interventions

All patients enrolled in the study will be hospitalized and will therefore receive monitoring by their physicians, nurses, respiratory therapists, and ancillary staff as a part of routine clinical care. A drug‐dispensing log will be kept current for each participant. This log will contain the identification of each participant and the date and quantity of drug dispensed. Under Title 21 of the Code of Federal Regulations (21CFR §312.62), the PI will maintain adequate records of the disposition of the investigational agent, including the date and quantity of the drug received, to whom the drug was dispensed (participant‐by‐participant accounting), and a detailed accounting of any drug accidentally or deliberately destroyed. Records for receipt, storage, use, and disposition will be maintained by the IDS and will be available for inspection.

#### Relevant concomitant care permitted or prohibited during the trial

Enrolled participants will not receive open-label citicoline during the 5-day intervention period. All other treatment decisions will be made by treating clinicians without reference to the protocol. Treatment of the underlying SARS CoV-2 viral infection is left to the discretion of the treating team. Depending on disease severity, and as based on current recommendations from the NIH, treatment may include but is not limited to antiviral therapy with remdesivir and administration of anti-inflammatory agents such as dexamethasone or tocilizumab. Patients deemed high risk for venothromboembolic disease may be treated with either prophylactic or therapeutic anticoagulation as appropriate. Other common medications such as vasopressors, sedative agents, antimicrobials, and neuromuscular blockade will be used in accordance with local standard of care in accordance with best practices.

Serious adverse reactions to citicoline have not been reported in the medical literature and are considered unlikely. Nevertheless, between randomization and day 5, study personnel will review the EMR daily for potential medication interactions with citicoline. There are no rescue medications for citicoline per se; however, reported side effects include headache, nausea, and low blood pressure. Rescue therapies for these side effects include (1) Analgesics for headache (acetaminophen, ibuprofen, rarely narcotics); (2) Antiemetics (ondansetron, metoclopramide); and (3) Fluid bolus for low blood pressure. Should a patient develop evidence of a severe reaction, resuscitation and treatment will be at the discretion of the treating physicians. Specifically, study drug will be discontinued at the time of suspicion of an adverse reaction. If anaphylaxis is suspected, the patient will receive epinephrine, anti‐histamines, and corticosteroids as appropriate. Resuscitation for hypotension will occur with fluids or vasopressor agents.

Rescue medications themselves can cause adverse reactions. Dexamethasone often causes transient hyperglycemia and may increase susceptibility to secondary infection of the lungs. Remdesivir may predispose to reversible transaminase elevation and case reports of bradycardia have been seen in post-market analysis. Mild transaminase elevation has been seen after administration of tocilizumab, so liver function monitoring is recommended. Immune suppression is expected following corticosteroid and tocilizumab dosing, and patients will be monitored for secondary bacterial infections.

#### On-study monitoring

Peripheral arterial O_2_ saturation (S_p_O_2_) will be monitored continuously and recorded every 2 min. Arterial blood gases will be measured on study days 1, 3, 5, and 8, or as clinically necessary.

Venous blood will be drawn at Time 0 and then once daily on study days 1–5 and 8 and processed by a research coordinator. At each study timepoint, a sufficient volume of venous blood will be drawn into blood container tubes containing appropriate anticoagulants to complete all the following assays: (1) CBC/differential count; (2) Hematology panel; (3) Clinical chemistry panels for renal, cardiac, and hepatic function; (4) Prothrombin Time and Partial Thromboplastin Time; (5) D-dimer, ferritin, fibrinogen; and (6) Thromboelastography. These assays will be performed by the clinical lab at the hospital in which that subject is located. All OSU hospital clinical laboratories are Clinical Laboratory Improvement Amendment-approved by the Dept. of Health and Human Services and are accredited by the College of American Pathologists’ Laboratory Accreditation Program. All clinical laboratory testing for study participants will comply with 42 CFR part 493.2 and 493.3(b)(2).

An additional 10 ml heparinized venous blood will be collected from each subject at each study timepoint for research purposes. Venous blood collected for research use from patients at both OSU East and OSU Main will be transferred to [name] laboratory in the Davis Heart and Lung Research Institute (part of OSU WMC and an approved research space). Plasma will be divided into 1-ml aliquots and stored in a locked − 80 °C freezer for batch analysis of biomarkers. Leukocytes will be resuspended in freezing media, aliquoted into cryovials, and stored at − 80 °C for downstream research studies.

Chest X-rays will be obtained on admission and subsequently when clinically indicated: for example, to confirm suspected secondary infections, etc. Chest X-ray is also routine after certain procedures (placing of central lines, intubation, thoracentesis, etc.). Subjective scoring by quadrants will be performed to determine whether this may be a useful secondary outcome measure for Phase 3 trials.

#### Biomarker analysis

Effects of citicoline on a variety of potential plasma biomarkers of ARDS and/or COVID-19 severity will be determined. Plasma IL-6, IL-8, IL-10, IL-18, and other cytokines and chemokines in plasma will be measured by Bio-Plex (48-Plex Human Cytokine Screening Panel). IFN-α, IFN-λ, Angiopoietin 2, C-reactive protein, lactate dehydrogenase, RAGE, and SP-D will be assayed using commercial ELISA kits. Plasma viremia, which has also been linked to prognosis [63, 64], will be quantified by qRT-PCR for SARS CoV-2 N gene using the CDC protocol. Batched assays will be performed in accordance with Good Laboratory Practice principles using validated commercial reagents. Residual samples will be retained in the − 80 °C freezer until conclusion of the study and analysis and then destroyed according to OSU protocol.

#### Outcomes

The primary goals of SCARLET are to establish the safety of citicoline in hospitalized SARS CoV-2-infected patients with HARF, to generate preliminary evidence of efficacy, and to identify an optimal citicoline dose for Phase 3 efficacy trials. There are therefore both safety- and efficacy-related primary outcome measures.

A particular dose of citicoline will be considered safe if the number of SAEs attributable to that citicoline dose (in the view of treating clinicians) remains below the threshold indicative of excessive toxicity once all 20 subjects have been treated (see Table 2).

**Table 2 Tab2:** Number of patients with SAEs required to claim excessive toxicity

No. of patients	1–2	3–4	5–7	8–10	11–14	15–17	18–20
No. with SAEs	–	2	3	4	5	6	7

The primary clinical outcome is a statistically significant difference in lowest recorded S_p_O_2_:F_i_O_2_ (S:F) ratio on study day 3, at *P* < 0.05. The lowest S_p_O_2_ for the day will be identified and used to generate the S:F ratio (based on the F_i_O_2_ at time of lowest S_p_O_2_ value).

Secondary/exploratory outcomes will be evaluated to identify statistically significant differences (*P* < 0.05) in (1) Lowest recorded S:F value on study days 1–2 and 4–8, or until extubation (whichever comes first); (2) Lowest Sequential Organ Failure Assessment (SOFA) score on study days 1, 3, 5, and 8; and (3) Highest COVID Ordinal Outcomes Scale score on study days 1, 3, 8, 15, and 29. On study day 29, we will also assess (1) Oxygen-free days through day 28; (2) Ventilator-free days through day 28; (3) ICU-free days through day 28; and (4) Hospital-free days through day 28.

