## Background

To date, there have been more than 100 million SARS CoV-2 coronavirus infections in the USA, resulting in more than 1.1 million deaths and counting. Effective vaccines are now available [1], but the virus continues to mutate and circulate within the population, and there is an ongoing risk of future severe pandemic waves.

Symptomatic SARS CoV-2 infection can progress to a clinical syndrome termed coronavirus disease of 2019 (COVID-19). Severe COVID-19 is characterized by acute respiratory failure and development of the acute respiratory distress syndrome (ARDS). COVID-19 may be complicated by coagulopathy, acute cardiac injury, renal injury, and other systemic manifestations [2–5]. Approximately 20% of all hospitalized patients [6] and up to 40% of those admitted to the intensive care unit (ICU) die [7]. Moreover, around 15% of survivors [8] develop “long COVID” [9], a disabling condition which is more likely after severe acute illness [10].

Treatment options for severely ill patients with COVID-19 are limited. Remdesivir, immunomodulators such as tocilizumab and baricitinib, and corticosteroids have been shown to be of some benefit and are currently recommended for use, but supportive ICU care remains central to managing these patients. Specifically, administration of high concentrations of supplemental O_2_ and mechanical ventilation are often required [11, 12]. Supportive care is resource-intensive, and interventions such as O_2_ therapy and mechanical ventilation can themselves be injurious to the lung [13, 14]. Additional therapeutics to manage patients with COVID-19 and reduce the need for ICU care are therefore urgently needed.

Approximately 50% of the epithelial cells lining the alveoli in the distal lung are small cuboidal ATII cells [15]. ATII cells regulate the depth of the alveolar lining fluid by alveolar fluid clearance [16]. They also synthesize, secrete, and recycle pulmonary surfactant proteins and lipids (including phospholipids), which help to maintain low alveolar surface tension [17], reducing dynamic alveolar collapse and preventing gas exchange impairment during ventilation. Surfactant phospholipids also have anti-inflammatory properties, and surfactant proteins play an important role in host defense against pathogens [18]. ATII cells are thus essential to normal lung function and host defense and play a central role in ARDS pathogenesis.

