#### Interim safety analysis

After enrollment of 8 subjects per group, an interim safety analysis will be performed based on a continuous safety monitoring rule to guide accrual suspension decisions based on unacceptable toxicity and SAEs. The number of patients with an SAE that would warrant temporary suspension of accrual in a given group corresponds to a high posterior probability that the true SAE probability is greater than an acceptable level (i.e., Pr($${p}_{i}$$ > 0.25 | data) > 0.85), where the posterior probability is determined from a Beta-Binomial distribution with Beta (1, 1) as the prior on $${p}_{i}$$. This is illustrated in Table 2.

For example, if 9 patients have been treated and 4 or more patients have an SAE, then accrual will be suspended while data are reviewed more closely and shared with the DSMB so that consensus regarding temporary suspension of accrual, protocol modifications, or decision to close the study early is made. Administration of the blinded study drug may be stopped temporarily or permanently for SAEs attributable to citicoline (in the view of the attending clinician) and in the event of clinical deterioration. In the latter case, the primary treating team is empowered to decide whether to stop the study drug and unblind group assignment. SAEs and unblinding will be recorded and reported to the DSMB at DSMB reviews and interim analyses.

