#### Frequency and plans for auditing trial conduct

The DSMB will review all safety data after the first 5 patients and at least yearly thereafter during planned DSMB Data Review Meetings. Data for the planned safety reviews will include, at a minimum, a listing of all reported AEs and SAEs, but access to primary data sources (e.g., the RedCAP database) will also be possible. Such data may be provided blinded by treatment group, with the understanding that unblinding may need to occur in a closed session of the DSMB. In addition, the DSMB will be informed of an Expedited Safety Report in a timely manner (within 14 days).

In addition to the pre‐scheduled data reviews and planned safety monitoring, the DSMB may be called upon for ad hoc reviews. The DSMB will review any event that potentially impacts safety at the request of the PI*.* In addition, the following events will trigger an ad hoc comprehensive DSMB Safety Review: (1) Any death that occurs in the study, which is possibly or definitely related to the study treatment regimen (to be reported within 24 h to DSMB); (2) SAEs that are possibly, probably, or definitely related to the study treatment regimen (reported within 24 h to DSMB); Any common trends in unexpected AEs (reported to DSMB within 5 business days). A temporary halt in study recruitment/randomization will be implemented if an ad hoc DSMB safety review is required. Subjects currently in study and tolerating therapy will be allowed to complete their 5-day course. After review of the data, the DSMB will make recommendations regarding study conduct and/or continuation.

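### A dose is called safe for not reaching a toxicity-detection boundary, so 6 of 20 patients with attributable SAEs would pass, and the sections using that boundary count different events

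*Protocol article*

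**What the plan says.** The Outcomes section makes safety one of the primary goals, with its own primary outcome measure. The quantity it counts is "the number of SAEs attributable to that citicoline dose (in the view of treating clinicians"). The dose earns the label 'safe' when this count "remains below the threshold indicative of excessive toxicity once all 20 subjects have been treated". The threshold is Table 2, whose title is "Number of patients with SAEs required to claim excessive toxicity". Its entries are 2 at 3–4 patients, 3 at 5–7, 4 at 8–10, 5 at 11–14, 6 at 15–17 and 7 at 18–20.

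The Interim safety analysis section gives the table's origin and a different use. It describes "The number of patients with an SAE that would warrant temporary suspension of accrual in a given group" as the number at which the posterior for the SAE probability satisfies Pr(p "> 0.25 | data) > 0.85", with a Beta(1, 1) prior. The analysis begins once 8 subjects per group are enrolled. The worked example is that "if 9 patients have been treated and 4 or more patients have an SAE, then accrual will be suspended". Neither the rule nor the example requires attribution to citicoline.

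Two other sections bear on the count. Recording of AEs gives the initial attribution to the PI, and the final one for safety reporting to the Medical Monitor, DSMB, PI and NIAID. Reporting of AEs and SAEs takes respiratory worsening consistent with COVID-19 progression out of the SAE category, unless there is evidence of a causal link.

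**The concern.** Table 2 asks whether the data show, with posterior probability above 0.85, that the SAE rate exceeds 25%. A count below it means only that this much evidence of toxicity was not obtained. Outcomes turns that absence of proof into a positive verdict, on a primary outcome, with 20 patients per dose. A dose could carry the label 'safe' into Phase 3 planning when the data favour a rate above the protocol's own acceptable level.

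The count itself is also unsettled. Outcomes counts SAEs, restricted to those that treating clinicians attribute to the drug. Table 2 and the interim rule count patients with an SAE of any cause. Attributable SAEs could be rare and any-cause SAEs common in hospitalized patients with respiratory failure, so one boundary will behave very differently under the two counts.

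**Working it through.** **Inputs.** Acceptable rate 0.25, posterior cut-off 0.85, Beta(1, 1) prior and start at 8 per group (Interim safety analysis); boundary values (Table 2); 20 patients per dose (Study design and setting).

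**1. Reproduce Table 2.** With x affected patients of n, the posterior is Beta(1 + x, 1 + n − x). The boundary is the smallest x with Pr(p > 0.25) > 0.85. This gives every Table 2 entry for n = 3 to 20. At n = 20:
- x = 6: Beta(7, 15), Pr(p > 0.25) = 0.744, below 0.85
- x = 7: Beta(8, 14), Pr(p > 0.25) = 0.870, above 0.85

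The table is computed correctly; the question is only how it is used.

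**2. What 'below the threshold' allows at n = 20.** Six of 20 passes.
- Observed rate: 6/20 = 30%, above the 25% acceptable level.
- Pr(p > 0.25) = 0.744, so Pr(p ≤ 0.25) = 1 − 0.744 = 0.256.
- Exact (Clopper–Pearson) 95% CI: 11.9% to 54.3%.
- Five of 20 also passes, with Pr(p > 0.25) = 0.567.

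**3. How often a dose is called safe, by true rate.** On the final count alone this is P(X ≤ 6) for X ~ Binomial(20, p). If 'remains below' also binds earlier looks, it is the probability, by exact recursion patient by patient, of never touching the boundary from n = 8 to n = 20.

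| True rate of the counted event | Final count only | Every look from n = 8 |
|---|---|---|
| 25% | 0.786 | 0.644 |
| 30% | 0.608 | 0.461 |
| 35% | 0.417 | 0.294 |
| 40% | 0.250 | 0.166 |

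**4. What is counted, side by side.**

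| Place | Unit | Which SAEs | Who attributes |
|---|---|---|---|
| Outcomes, definition of safe | SAEs | attributable to the dose | treating clinicians |
| Table 2 title | patients | any | – |
| Interim safety analysis, rule and example | patients | any | – |
| Recording of AEs | – | – | finally the Medical Monitor, DSMB, PI and NIAID, for safety reporting |

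**5. Why the choice matters.** Take the any-SAE count, no drug effect, and looks at every patient from n = 8. The background rates are assumptions, since the article gives no expected SAE rate.
- 20%: one arm crosses with probability 1 − 0.808 = 0.192; at least one of four, 1 − 0.808⁴ = 0.573.
- 30%: one arm, 1 − 0.461 = 0.539; at least one of four, 1 − 0.461⁴ = 0.955.

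If the table is applied only once, at n = 8 (boundary 4), one arm crosses with probability 0.056 at 20% and 0.194 at 30%.

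**The case against.** Several points on the other side stand.

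- **Table 2 is sound as a monitoring rule**, and its consequence is a temporary suspension with DSMB review, not termination.
- **Six attributable SAEs would not go unreviewed.** Under Frequency and plans for auditing trial conduct, a possibly related SAE triggers an ad hoc DSMB review, and "A temporary halt in study recruitment/randomization will be implemented if an ad hoc DSMB safety review is required". A reader might infer that this conflicts with Table 2. It does not: one rule is driven by single events and the other by a cumulative count per arm, and both can operate. But these reviews do not alter the definition of safe.
- **The scenario may be remote.** The Discussion describes adverse effects of citicoline as very rare, below 1 in 10,000. That makes 6 of 20 attributable SAEs unlikely if the expectation is right, but the criterion is there for the case where it is wrong.
- **Background illness alone need not suspend accrual.** A reader might infer that it would, since the Background section says "up to 40% of those admitted to the intensive care unit (ICU) die". That figure concerns ICU patients; the same sentence gives about 20% for all hospitalized patients. Imminent death, ECMO and multiple organ failure are exclusions, and COVID-consistent respiratory worsening is not an SAE. The 20% and 30% rates above are therefore illustrations, not forecasts.
- **Attribution for safety reporting may serve a different purpose** from attribution for the outcome. If so, the article should say so.
- **A placebo comparison of SAEs is ordinary analysis-plan content**, and the reporting section already accepts an aggregate comparison with controls as evidence of causality. Its absence from this article is not itself an error.

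**Conclusion.** The point holds. The Outcomes criterion cannot support the word 'safe': it passes a dose at 6 of 20, where the posterior probability of exceeding the protocol's own 25% level is 0.74. It passes a dose with a true 35% or 40% rate 42% or 25% of the time on the final count, or 29% or 17% if every look from 8 patients binds. These figures assume that patients are counted, with independent events at a constant rate. If SAEs were counted instead, six patients with seven or more SAEs between them would fail.

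The conflict over which SAEs are counted, and in what unit, is on the face of the text. It matters most under the any-SAE count. There an arm with no drug effect crosses with probability 19% or 54% at assumed background rates of 20% or 30%, and at least one of four arms does so with probability 57% or 95%. These depend on the assumed rates and on looks at every patient from n = 8.

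A reader might also infer that the plan's limits should simply be reversed, requiring Pr(p < 0.25) > 0.85, which allows at most 2 of 20. The documents set no such standard. Under any-SAE counting it would be met only 21% of the time at a 20% background rate, with no drug effect at all.

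**What to change.** 1. Keep Table 2 for accrual review only.
2. Replace the 'considered safe' conclusion with 'toxicity boundary not reached', reported for each dose with the posterior Pr(rate > 0.25) and an exact confidence interval. Alternatively, claim safety only on a positive-evidence criterion that the sponsor prespecifies for the event finally counted.
3. Count patients, not events, as Table 2 does.
4. Reconcile Outcomes, Recording of AEs and Interim safety analysis on which SAEs count and who attributes them, and state whether 'remains below' binds the earlier looks.
5. Report each dose's all-cause SAE risk difference from the concurrent placebo arm with a confidence interval, so that the safety reading does not rest on causality judgments alone.

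The cost is a change of wording and a few added summaries, with no new data or patients. The price is a weaker safety statement at 20 patients per dose, which is what that number can support.
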